### Randomisation

If the participant consents to participate in Phase 2, they will be randomly allocated to one of the two trial arms (open randomisation; ratio 1:1) by the King’s Clinical Trials Unit (KCTU), King’s College London. The randomisation procedure will be a stratified block randomisation. Centres will be blocked to ensure that there are equal participants in each arm at each site. The randomisation schedule will be incorporated into a dedicated electronic database and kept securely within this electronic system, inaccessible to the enrolment location. Once an eligible participant has given written informed consent and completed the baseline assessment, the RA will log on to the randomisation system, enter the participant identification number and hospital, and will click on the ‘randomise’ function. The treatment allocation will appear immediately on screen and be communicated to the patient. The confirmation of treatment allocation details will be sent to the research team immediately. The RA will inform the participant’s HIV clinical team on the same day. Movement from the observational cohort to the intervention trial or declining participation in the trial will be recorded on the central database.

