#### Phase 2 – trial

Since this study uses a novel measure combining both uptake and adherence, there are no data to inform a sample size calculation. It is plausible that the distribution could be bimodal or highly skewed. As the proportion with ≥90% adherence will also be bounded by [0,1], standard sample size calculations based on the normal distribution would likely be inappropriate, even if a standard deviation could be hypothesised. This study therefore defines a good primary outcome as ≥80% of follow-up months with ≥90% adherence. Since the study selects for an at-risk group, we would expect a large difference between control and intervention groups, and a 15% difference between groups is considered clinically significant based on estimated intervention costs. Table 1 shows the number of participants needed in each arm to detect a 15% difference in adherence from a range of possible control group percentages with > = 0.8 of follow-up months with ≥90% adherence (80% power, 2-sided alpha = 0.05). We will therefore recruit 372 participants.

**Table 1 Tab1:** Sample size calculations for Phase 2 – trial

Standard of care group % with > 0.8 of follow-up months with ≥90% adherence	Intervention group % with > 0.8 of follow-up months with ≥90% adherence	N per arm	Total N
35%	50%	183	366
45%	60%	186	372
50%	65%	183	366
60%	75%	165	330
70%	85%	134	268

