### Statistical methods and analysis

The SUPA intervention is hypothesised to be superior to care as usual, and therefore the planned analysis is intention to treat, including all randomised participants, with all participants analysed according to the study group to which they were randomised regardless of subsequent treatment received. Primary analysis will include all randomised participants other than those randomised in error (defined as not intending to randomise the participant through e.g. miscommunication, rather than a participant or clinician decision once the allocation has been given).

A per-protocol analysis will be carried out on the primary endpoint including all participants in the intervention group who attended all 4 (2 + 1 + 1) sessions. If the intention to treat and per-protocol analyses on the primary endpoint leads to inconsistent results, then per-protocol analysis will also be carried out on all the other endpoints.

Continuous variables will be summarised by medians and IQRs or means and standard deviations as appropriate depending on the distribution, and compared between groups using ranksum tests or t-tests respectively. Comparisons of change from baseline in continuous variables will adjust for any baseline imbalances using either quantile or normal linear regression (depending on the shape of the distribution).

Categorical variables will be summarised by frequency tables, and compared between groups using chi-squared tests, unless any cell count is < 5 or cell percentage is < 5% in which case exact tests will be used. Binary variables will be summarised by percentages, using standard exact 95% CI for the risk differences. Time-to-event variables will be summarised using Kaplan-Meier curves and average differences between randomised groups estimated using Cox models. Patients without the event recorded will be censored at their last clinic visit. Proportionality of hazards will be tested; where significant departures exist, varying differences between randomised groups over time will be estimated using flexible parametric models of Royston and Parmar. Rate of treatment switching will be analysed using Poisson regression, including all changes to ART as events and the total time under follow-up through the earliest of 12 months or the last patient visit as the person-time at risk. Primary analysis will not stratify by clinical centre.

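### Randomisation is blocked within centre but the primary analysis leaves centre out without a stated reason: a possible small loss of efficiency, not a bias

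*Protocol article*

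**What the plan says.** The Randomisation section sets the design: "The randomisation procedure will be a stratified block randomisation", with "open randomisation; ratio 1:1". Centre is the stratifying factor: "Centres will be blocked to ensure that there are equal participants in each arm at each site". The Setting section lists eight hospitals.

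Statistical methods and analysis gives the methods for categorical and binary variables. Groups are "compared between groups using chi-squared tests, unless any cell count is < 5" (or a cell percentage is below 5%), in which case exact tests are used. Binary variables are summarised by percentages, "using standard exact 95% CI for the risk differences". The section closes with "Primary analysis will not stratify by clinical centre". No reason follows, and no centre-adjusted analysis is mentioned anywhere in the article.

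The sample size section for the Phase 2 trial assumes a plain comparison of two proportions ("80% power, 2-sided alpha = 0.05") and says that "a 15% difference between groups is considered clinically significant". The row of Table 1 that sets the total is 45% against 60%, with 186 per arm and 372 in all.

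**The concern.** Blocking within centre gives each arm nearly the same mix of centres. Differences in outcome between centres then largely cancel out of the comparison of arms, so its true variance depends mainly on variation within centres. An unstratified two-proportion test takes its variance from the pooled success rate, which still includes the variation between centres. If centres differ, the standard error is too large, the interval too wide and the test slightly conservative.

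Centre could matter for this endpoint. The Primary endpoint section counts each day before ART starts as 0% adherence, so the result depends partly on how quickly patients start. The usual-care section allows for slight variation between clinics. At stake is precision that the randomisation scheme makes available and the analysis does not use.

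**Working it through.** **Inputs from the article.** Eight centres, 1:1 blocks within centre, 372 participants, 45% against 60%, two-sided alpha 0.05, 80% power.

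**Assumptions.** The article gives neither the between-centre spread nor the centre sizes. The spread is varied below as a between-centre SD of the success rate from 0 to 0.20. Centre sizes are taken as 90, 70, 50, 45, 40, 35, 26 and 16 (sum 372).

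**1. The plan's own figure.** Without continuity correction:

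n = [1.96√(2 × 0.525 × 0.475) + 0.8416√(0.45 × 0.55 + 0.60 × 0.40)]² / 0.15² = 172.8, so 173 per arm.

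With the correction: (172.8/4) × [1 + √(1 + 4/(172.8 × 0.15))]² = 185.9, so 186 per arm. The corrected formula reproduces all five rows of Table 1 (183, 186, 183, 165, 134). At 186 per arm, the uncorrected test has power Φ[(0.15 − 1.96 × 0.05178)/0.05120] = 82.8%.

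**2. Mechanism.** Let n be the number per arm, w_j the share of participants in centre j and p_j its success rate, with no treatment effect.

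- Variance used by the unstratified test: (2/n) p̄(1 − p̄)
- Variance under balance within centre: (2/n) [p̄(1 − p̄) − Σ w_j (p_j − p̄)²]

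The ratio of the second to the first is 1 − ICC, where ICC is the between-centre variance divided by p̄(1 − p̄). The unstratified standard error is therefore too large by a factor 1/√(1 − ICC), and the realised alpha is 2[1 − Φ(1.96/√(1 − ICC))].

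| ICC | SE too large by | Realised alpha | Power, unstratified | Power, stratified |
|---|---|---|---|---|
| 0 | 0% | 5.0% | 82.8% | 82.8% |
| 0.02 | 1.0% | 4.8% | 83.1% | 83.6% |
| 0.05 | 2.6% | 4.4% | 83.5% | 84.7% |
| 0.10 | 5.4% | 3.9% | 84.1% | 86.6% |
| 0.20 | 11.8% | 2.8% | 85.5% | 90.2% |

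To convert an SD to an ICC at a mean of 52.5%, divide SD² by 0.525 × 0.475 = 0.2494. An SD of 0.10 gives 0.04, 0.15 gives 0.09 and 0.20 gives 0.16.

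**3. Simulation.** There were 60,000 trials per scenario, with rates centred on 52.5%. The unstratified chi-squared test is compared with Cochran-Mantel-Haenszel (CMH), both without continuity correction.

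| Between-centre SD | Type I error, unstratified | Type I error, CMH | Power, unstratified | Power, CMH |
|---|---|---|---|---|
| 0 | 5.5% | 5.2% | 83.8% | 83.3% |
| 0.10 | 5.0% | 5.1% | 84.3% | 84.5% |
| 0.15 | 4.5% | 5.0% | 84.8% | 86.0% |
| 0.20 | 3.8% | 5.0% | 85.9% | 88.5% |

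The simulated loss of alpha is milder than the formula gives, for two reasons. The uncorrected test starts slightly above 5% (5.5%) at this sample size because the data are discrete. With only eight centres, the expected spread within a trial is also smaller than the assumed SD: the variance is multiplied by 1 − Σw_j² = 1 − 21,282/138,384 = 0.846.

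The power figures at SD 0.20 depend on how extreme centre rates are bounded. Another run at the same centre sizes gave 84.5% against 87.5%, so the gain there is 2.6 to 3.0 points.

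**4. With a continuity correction.** The article does not say whether the chi-squared test is corrected. In a separate set of simulations with other assumed centre sizes and with blocks of 4, the corrected unstratified test had power of 81% to 83%, still above 80%.

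**The case against.** The strongest case against the point is that nothing in the article shows centre to be prognostic. The same sentence that allows slight variation in usual care also says that all sites share one framework. Sites were chosen on a single common ground, suboptimal attendance after diagnosis, and every trial participant passes the same risk threshold on the beliefs questionnaire. A visible effect needs wide spreads. Taking two SDs either side of 52.5%, an SD of 0.15 means centres from about 22% to 82%, and 0.20 means about 12% to 92%. At 0.10, already about 32% to 72%, stratifying gains nothing that matters. The sample size was also set for an unadjusted comparison, so no planned power is forgone. The quoted sentence covers only the primary analysis, and an analysis plan not shown here may contain a centre-adjusted sensitivity analysis.

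All of this stands. It limits the size of the point and makes it conditional. It does not supply a reason for leaving out the stratifying factor, and stratifying keeps the error rate near 5% across the whole range.

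A reader might infer more than the article supports:

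- **Bias or an inflated error rate.** Neither follows. Blocking keeps the arms comparable, and ignoring centre moves the error rate down.
- **An underpowered trial.** Unstratified power exceeds 80% in every scenario run.
- **Intervals that are certainly too wide.** That depends on a between-centre variance that the article does not give. The article also plans exact intervals, which these simulations did not evaluate.
- **A need for centre in the subgroup logistic models.** No calculation here bears on that.

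**Conclusion.** The point holds as a minor one. The article makes an explicit choice that leaves its own stratifying factor out of the primary analysis, and it gives no reason. If centre is prognostic, the unstratified analysis is mildly conservative and gives up some efficiency. The loss is practically nil up to a between-centre SD of about 0.10. At 0.15 it is about half a point of type I error and one point of power; at 0.20 it is about 1.2 points of type I error and 2.6 points of power in the main simulation. These sizes rest on the assumed spread and centre sizes. The direction is certain if centres differ; whether they differ, and by how much, cannot be settled from the article.

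**What to change.** Replace the sentence that excludes centre with wording such as:

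> The primary comparison will be a Cochran-Mantel-Haenszel test stratified by clinical centre, reported with a Mantel-Haenszel risk difference and 95% CI. The unstratified chi-squared test and exact interval will be reported as a sensitivity analysis.

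If the sponsor prefers to keep the unstratified analysis as primary, one line should say why.

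The change needs no new data and leaves the sample size at 372. Mantel-Haenszel weights cope with small centres. If centres do not differ at all, the cost is at most about half a point of power (83.3% against 83.8%). The Trial status section reports that no data cleaning or analysis had been done at submission, and the Discussion says that the statistical team is blinded. The change should be dated and made before any unblinded outcome data are seen.

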### Subgroup analyses

Subgroup analyses will be performed to assess heterogeneity in differences between randomised groups for the primary endpoint according to gender, ethnicity, number of intervention sessions attended, early (treatment indicated at point of diagnosis) vs late diagnosis (treatment not indicated at point of diagnosis), starting for clinical need vs starting for treatment as prevention, baseline CD4 count, and baseline BMQ scores - low Necessity vs high Concerns vs both low Necessity and high Concerns. Subgroup analyses will use logistic regression to model interactions between randomised group and the factors above.

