## Methods

### Study design

This study comprises 2 phases (Fig. 1). Phase 1 is an observational cohort study, in which PLWH who are ART naïve and recommended to take ART by their clinician complete a questionnaire assessing their beliefs about ART over a period of 12 months. Phase 2 is a randomised controlled trial (RCT) nested within the observational cohort study to investigate the effectiveness of the SUPA intervention on adherence to ART and to explore the intervention mechanism. PLWH who are at risk of nonadherence will be recruited and randomised 1:1 to the intervention and control arms. All participants will receive usual care which is provided to all NHS patients through clinical support from a multi-disciplinary healthcare team including the patient’s assigned HIV physician, nurses, pharmacists and other healthcare professionals, such as clinical psychologists, as required. In addition, participants in the intervention arm will receive the SUPA intervention.

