### Intervention: SUPA intervention + care as usual (CAU)

The SUPA intervention has been described in detail in a separate publication ([name], [name], [name], [name], [name], [name]: SUPA Group. The development of an intervention to support uptake and adherence to antiretroviral therapy in people living with HIV: the SUPA intervention, submitted). Patients randomised to the intervention group will receive treatment initiation support within 1 month of enrolment into the intervention trial. This support will be in the form of 4 tailored treatment support sessions delivered by a Research Nurse (RN) utilising a collaborative Cognitive Behavioural Therapy (CBT) and Motivational Interviewing (MI) approach. The sessions will be conducted face-to-face (or by telephone if the patient prefers or cannot meet face to face) and will communicate a rationale for the personal necessity of medication, elicit and address concerns about medication and problem-solve potential practical barriers to adherence. Sessions will be tailored to individual needs and preferences, based on (1) the individual patient’s perceptions and practical barriers to ART identified using the BMQ-ART, and (2) salient issues arising during the sessions. An animation series and intervention manual have been developed as tools to communicate a rationale for the personal necessity of ART and to illustrate concerns and potential solutions. The specific timing of the sessions will differ according to the patient’s specific needs and availability; however, the first two sessions will take place within 1 month of enrolment, and sessions 3 and 4 will provide additional support 3 and 6 months post randomisation. These appointments will be scheduled at the patient’s convenience.

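### The planned interaction between randomised group and sessions attended cannot be estimated, because controls have no sessions; what could be fitted in its place is open to confounding.

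*Protocol article*

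**What the plan says.** All references are to the protocol article.

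- **Subgroup analyses.** The aim is to "assess heterogeneity in differences between randomised groups for the primary endpoint". Seven factors are listed: gender, ethnicity, "number of intervention sessions attended", early or late diagnosis, "starting for clinical need vs starting for treatment as prevention", baseline CD4 count and baseline BMQ pattern. The method sentence covers the whole list: "Subgroup analyses will use logistic regression to model interactions between randomised group and the factors above". Sessions attended is not excepted.
- **Study design.** All participants receive usual care. "In addition, participants in the intervention arm will receive the SUPA intervention". The section on the control arm includes no SUPA session.
- **Intervention section.** Four sessions are planned. Of these, "the first two sessions will take place within 1 month of enrolment", and the third and fourth are placed at 3 and 6 months after randomisation. Under Participant follow-up, the first session is part of the baseline visit, which also includes randomisation.
- **Primary endpoint.** Adherence is computed month by month from randomisation. A good outcome is at least 90% adherence in at least 80% of the follow-up months.

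**The concern.** A subgroup interaction asks whether the difference between arms varies across levels of a factor. Each level must therefore contain participants from both arms. Sessions attended has no such levels: a control participant cannot have attended one, two, three or four sessions. The model as written has no answer to return.

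The practical risk lies in what is reported in its place. Software will usually drop the redundant term and print a coefficient for sessions. That coefficient looks like a dose-response estimate, but it compares people who chose to attend with people who did not, during the period in which the outcome is being counted. Session delivery is a main component of intervention cost under Health economic analyses, so an apparent gradient could be read as support for delivering more sessions.

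**Working it through.** **1. Sample size used in the check.** The largest row of Table 1 is 45% vs 60%, with 186 per arm (two-sided alpha 0.05, power 80%).

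- Uncorrected: n = [1.95996·√(2·0.525·0.475) + 0.84162·√(0.45·0.55 + 0.60·0.40)]² / 0.15² = (1.38417 + 0.58763)² / 0.0225 = 172.8, that is 173.
- Continuity-corrected: n′ = (172.8/4)·[1 + √(1 + 4/(172.8·0.15))]² = 43.2·(2.07439)² = 185.9, that is 186.

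The other four rows also reproduce with the correction (183, 183, 165, 134). No figure in Table 1 is in dispute; 186 per arm is carried forward.

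**2. Is the interaction identifiable?** Let A = 1 for intervention and 0 for control, and let S = sessions attended.

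- *S numeric, controls coded 0.* The columns are 1, A, S, A×S. For controls A×S = 0 = S; for intervention participants A×S = S. The last two columns are identical: rank 3 of 4.
- *S as categories 0 to 4.* The columns are 1, A, four indicators and four products. Each product equals its indicator: rank 10 − 4 = 6 of 10.
- *S missing for controls.* Only the intervention arm remains, so A equals the intercept and A×S equals S: rank 2 of 4.

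The interaction has no separate estimate under any of these codings, at any sample size.

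**3. What is left to fit.** With S numeric and the redundant term dropped, the intercept fits the controls, and A and S together fit the intervention arm. The coefficient of S is then a slope within the intervention arm. With S as categories, the fitted values allow each attendance group to be set against all controls.

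**4. Overlap of attendance and outcome.** Over 12 months the threshold is 0.8 × 12 = 9.6, so 10 good months are needed. Three failed months leave at most 9, and the outcome is then already poor. This can happen by month 3, before the session planned at 6 months. Later attendance can therefore follow from the outcome as well as precede it.

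**5. How large could a false gradient be?** This was simulated with no intervention effect, 186 per arm and 2,000 runs per setting. The documents give no attendance or prognosis figures, so all of the following are assumptions:

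- Prognosis u is standard normal.
- The log-odds of a good outcome are −0.22 + 1.0·u in both arms, giving about 45% in controls.
- Sessions in the intervention arm are binomial out of 4, with log-odds 1.0 + γ·u.
- The fitted model is logistic on arm and sessions.

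| Link γ (log-odds per SD) | Sessions term p < 0.05 | Median odds ratio per session | Good outcome: all 4 sessions | Good outcome: 2 or fewer | Controls |
|---|---|---|---|---|---|
| 0 | 4.8% | 1.00 | 45.6% | 45.3% | 45.3% |
| 0.5 | 61.8% | 1.44 | 55.4% | 35.3% | 45.4% |
| 1.0 | 95.7% | 1.68 | 60.6% | 30.3% | 45.3% |

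Set against controls, the attendance groups differ by about +10 and −10 points at γ = 0.5 (55.4 − 45.4; 35.3 − 45.4) and by about +15 and −15 points at γ = 1.0 (60.6 − 45.3; 30.3 − 45.3). The true effect is zero throughout.

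**The case against.** The other side has several good points.

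- **Reach.** This is one of seven factors in a secondary analysis. The primary comparison is by randomised group and does not use attendance, and the sample size does not depend on it. This stands and limits the severity.
- **Certainty of a false dose response.** A reader might infer that the analysis is bound to produce one. The document does not support that: the bias needs attendance to be related to prognosis, and no figure for this is given. With no link the false-positive rate is nominal. The link is plausible, because attending sessions and taking tablets are behaviours of the same person, but its size is unknown.
- **Comparison with controls.** A reader might infer that any output sets self-selected attenders against controls. With numeric coding it does not; it is a slope within the intervention arm.
- **Clinical need vs treatment as prevention.** The word *starting* might suggest that this factor is known only for people who start ART, so that never-starters have no category and the factor conditions on the outcome. Inclusion criterion 4 requires a recommendation to start ART before enrolment, so a reason can be recorded at baseline for everyone. This is loose wording, not a demonstrated error.
- **Early vs late diagnosis.** The labels might seem reversed. The article defines both categories where it lists them and gives no competing definition. Swapping the labels would change neither the interaction test nor the two subgroup estimates.

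The non-identifiable interaction is untouched by these points. It also cannot be set aside as detail left to an analysis plan, because the article itself states the model and applies it to every listed factor.

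**Conclusion.** The point holds for sessions attended. The stated interaction is not identifiable, and this follows from the design alone, without any assumption. The reduced models that could stand in for it are confounded if attendance is related to prognosis. Over the assumed range of 0 to 1.0 log-odds per SD, the chance of a significant sessions term with no intervention effect runs from about 5% to about 96%. That range is illustrative: it rests on the assumed attendance distribution and the assumed strength of prognosis.

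The effect is confined to a secondary analysis. The other six subgroup factors can be kept, one of them with a clarification of wording. Severity: should be fixed.

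**What to change.** 1. Delete sessions attended from the subgroup interaction list, and state that interaction tests are restricted to factors fixed at baseline.
2. If outcome by sessions attended is of interest, report it as a descriptive summary within the intervention arm, labelled as non-causal.
3. A complier-type analysis with randomisation as the instrument is optional. If used, it should state how compliance is defined and which exclusion or linearity assumption it relies on. The definition matters: the first session is at the baseline visit, so counting any attendance as compliance would probably return something close to the intention-to-treat effect. Requiring all four sessions would strain the exclusion assumption, because partial attenders are also treated.
4. Minor wording: state that clinical need vs treatment as prevention means the reason for the recommendation recorded at baseline.

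The cost is wording only. No participants, extra data or change of sample size are needed, and Trial status reports that no data cleaning or analysis had been done when the article was submitted.
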